## Abstract

**Background:**

Peripheral venous catheters are the most commonly used invasive devices in hospitals worldwide. Patients can experience multiple adverse events during the insertion, maintenance, and management of these devices. Health professionals aim to resolve the challenges of care variability in the use of peripheral venous catheter through adherence to clinical practice guidelines. The aim of this cluster-randomized controlled trial is to determine the efficacy of a multimodal intervention on incidence of adverse events associated with the use of peripheral venous catheters in adult hospital patients. Additional aims are to analyze the fidelity of nurses and the relationship between contextual factors on the use of best available and the outcomes of the intervention.

**Methods:**

Five public hospitals in the Spanish National Health System, with diverse profiles, including one university hospital and four second-level hospitals, will be included. In total, 20 hospitalization wards will be randomized for this study by ward to one of two groups. Those in the first group receive an intervention that lasts 12 months implementing evidence-based practice in healthcare related to peripheral catheters through a multimodal strategy, which will contain updated and poster protocols insertion, maintenance and removal of peripheral venous catheters, technologies applied to e-learning, feedback on the results, user and family information related to peripheral catheter, and facilitation of the best evidence by face-to-face training session. Primary outcome measures: Incidence of adverse events associated with the use of peripheral venous catheters is measured by assessing hospital records. Secondary outcome measures: Nurses’ adherence to clinical practice guidelines, clinical outcomes, and the cost of implementing the multimodal intervention.

**Discussion:**

Clinical implementation is a complex, multifaceted phenomenon which requires a deep understanding of decision-making, knowledge mobilization, and sense making in routine clinical practice. Likewise, the inclusion of strategies that promote fidelity to recommendations through multicomponent and multimodal intervention must be encouraged. The use of a transfer model could counterbalance one of the greatest challenges for organizations, the evaluation of the impact of the implementation of evidence in the professional context through quality indicators associated with prevention and control of infections.

**Trial registration:**

Current Controlled Trials ISRCTN10438530. Registered 20 March 2018.

## Background

Peripheral venous catheters (PVC) are the most commonly used invasive devices in hospitals worldwide [1]. Patients can experience multiple adverse events such as phlebitis, extravasation, or infections during the insertion, maintenance, and management of these devices [2]. Among these adverse events, catheter-related bloodstream infections (CRBSI) are catastrophic [3] yet potentially preventable episodes [4]. The incidence of PVC-associated bloodstream infections (PVC-BSI) is between 0.1 and 0.5 per 1000 catheter days [5]. CRBSIs can prolong length of hospital stay [2, 6] and carry an attributable mortality rate of up to 25% [7, 8]. The approximate average cost per episode of CRBSI is $45,000 and thus resulting in $2.3 billion of unnecessary expenditure per year in the USA [3].

The genesis of evidence-based clinical practice (EBCP) is the integration of best available scientific knowledge in combination with clinical experience and user preferences on health and care issues [9–11]. Clinical practice guidelines (CPGs) are based on empirical evidence, developed critically with explicit methods by experts, free of conflicts of interest and with specific and unambiguous recommendations [12]. These guidelines are developed to assist the decision-making of health professionals and patients about appropriate health care interventions in specific clinical circumstances. However, CPGs are not exempt from challenges [13]. The number of guidelines has grown significantly and thus the volume of evidence proven to be unmanageable and of variable quality [14]. Additionally, there is frequent tardiness in the implementation of the recommendations within the CPGs, probably fueled by perceptions of clinical judgment as the main element in clinical decision-making [15]. These facts can ultimately weaken the credibility of CPGs and therefore increase the difficulty of their implementation [16].

In the last decade, healthcare systems have also focused on reducing the variability of healthcare practice [17]. International research agencies have conducted strategies to effectively implement knowledge to resolve the challenges presented by clinical practice variability and offer optimal, quality care to patients and citizens [18].

However, the introduction of innovations into daily clinical practice remains arduous. Despite efforts to reduce the research-practice gap, some studies suggest that 30–40% of patients are still not offered care based on best available evidence [19, 20]. Such gap is therefore a major threat to patient safety and healthcare efficiency [21]. The use of implementation models aims to enable the integration of key elements which are in permanent and dynamic interaction, such as research result innovations, the individuals and teams that have to enact the change and local and organizational context, which will be supported through the process of facilitation to warrant effective knowledge mobilization (EKM) [22–27]. Therefore, the incorporation of a knowledge mobilization model could be a feasible approach to reduce such research-practice gap that it embed a deep understanding of decision-making and key elements to promote adherence of evidence-based practice [28].

This protocol describes a theoretical model to evaluate the effectiveness of a multimodal intervention focused on implementing evidence into clinical practice. Drawing from the core elements of evidence, context, and facilitation present on The Promoting Action on Research Implementation in Health Services (PARIHS) framework, we will determine the efficacy of our planned intervention on the incidence of adverse events associated with the use of PVC in adult patients in hospital. This research will also unpack the relationship between factors influencing local context and individual perceptions about the use of evidence-based practice.

## Methods/design

### Aims

To determine the efficacy of a multimodal intervention to reduce the incidence of adverse events (CRBSI, extravasation, obstruction, and phlebitis) associated with the use of PVC in adult patients in hospital.To analyze the fidelity of nurses to the recommendations within the CPG for insertion and management of PVCs.To associate post-intervention adverse event rates with contextual and individual factors on the use of best available knowledge in clinical practice decisions.

### Primary hypothesis

The implementation of a multimodal intervention will decrease the incidence of adverse events (CRBSI, extravasation, obstruction and phlebitis) associated with the use of PVCs in adult patients in hospital.

### Secondary hypotheses

Nursing practice outcomes: An optimal fidelity of nurses to the recommendations within the CPG for insertion and management of peripheral venous catheter in hospital wards receiving the intervention will translate into reduced care variability, increased documentation about PVC use in nursing records and greater requests of catheter tip culture from PVCs removed from patients experiencing adverse events.Clinical outcomes: The fidelity of nurses to the recommendations within the CPG for insertion and management of peripheral venous catheter in hospital wards receiving the intervention will reduce unnecessary PVCs and decrease hospital length of stay (HLOS).Health economic outcomes: The implementation and development costs of the intervention will be offset by savings from decreased incidence of CRBSIs and HLOS.EBCP environment: The contextual and individual factors on the utilization of knowledge in clinical practice decisions and impact on hospital ward processes and practice measured by Nursing Work Index (NWI) [29] and Evidence-Based Practice Questionnaire (EBPQ) [30].

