### Primary outcome measures: effect evaluation

The primary outcome will be the incidence of adverse events associated with the use of PVCs in adult inpatients. This incidence will be determined from evaluation of hospital records at 3, 6, 9, and 12 months.

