### Secondary outcome measures: process evaluation

Nurses’ adherence to CPGs will be measured at 3, 6, 9, and 12 months with the following subcategories:1.1Multimodal intervention content will be delivered as planned (yes/no), and dosage will be delivered as often and long as planned (yes/no); face-to-face training session will be assessed by measuring the number of nurses who completed the Masterclass at the intervention phase. Feedback will be evaluated by checking the distribution of clinical audit results within intervention wards. Patient information will be assessed by monitoring the presence of informative leaflets on the ward (yes/no) and asking if the patient is aware of use of PVC and prevention recommendations for personal care. Facilitation will be measured by number of internal facilitators who completed the intervention.Clinical audits on use of PVC. Device utilization ratios will be measured by percentage of PVCs per hospital wards and number of PVC per patient. Documentation of PVC in nursing records will be assessed by percentage of fully completed records. PVC maintenance will be monitored by random, monthly clinical audits, which will document PVC size (16/18/20/22/24 gauge), site (dorsum of hand/forearm/antecubital region/upper arm), dressing integrity (clean/dry/intact), securement and time in situ (less 48 h/ between 48 and 96 h/more 96 h). Catheter tip will be measured by number of catheter tip extraction following removal of PVCs.Routine practice. Clinical effectiveness questionnaire for the prevention of PVC complications will be completed pre and post intervention. The questionnaire is made up of 35 questions in four sections, relating to general asepsis and skin antisepsis; PVC insertion, maintenance, and removal; PVC documentation; and patient and professional education.Clinical outcomes will be assessed using rates of unnecessary PVCs, rates of CRBSI, extravasation, obstruction and phlebitis, defined as per standard guidelines, and mean HLOS associated to PVC-BSIs at 3, 6, 9, and 12 months.The direct costs of implementing the multimodal intervention will be assessed using HLOS for patients and decrease rates of adverse events at 12 months (post intervention).EBCP environment:EBCP context: The contextual factors on the utilization of knowledge in clinical practice decisions and impact on hospital ward processes and practice will be assessed using the NWI tool pre-intervention. The variables are summarized into five main groups: nurses’ participation in hospital affairs; quality of nursing care; nurse management’s capacity, leadership, and support for nursing staff; size of the nursing workforce and adaptation of available human resources, and professional relation between doctors and nurses.EBCP individual: The opinions, attitudes, abilities and motivations of nurses and their links with the development of a culture of clinical practice based on the transfer of new knowledge to the healthcare given to patients will be assessed using EBPQ pre-intervention. The questionnaire is made up of 24 questions relating to professionals’ knowledge, use and attitudes towards EBCP.

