### Intervention group

The intervention will last 12 months and will be based on a theoretical model on effective knowledge mobilization, integrating a multimodal strategy related to peripheral catheters clinical practice improvement which includes the following (Fig. 1): (1) implementation of recommendations trough up-to-date protocols and posters related to hand hygiene and aseptic measures, insertion, maintenance and removal of PVC [34]; (2) use of e-learning technologies [35–37]; (3) feedback on the results and messages addressed to healthcare professionals to facilitate adherence to recommendations [38]; (4) face-to-face training sessions [39]. Masterclass related to PVC insertion, maintenance, and removal will consist of information shared about recommendation of CPGs adapted according to the needs detected by means of the questionnaire on the effectiveness of the healthcare practice; (5) leaflets with information for patients and family/careers about peripheral catheters, in appropriate language [40]; and (6) support by internal facilitators, which will be key members of staff in the organizations, to adopt best evidence based on the PARIHS theoretical model [26, 41, 42].

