**Fig. 1 Fig1:**
[figure not shown]
Theoretical model on effective knowledge mobilization

This facilitation will be carried out by nurses using the Facilitating Implementation of Research Evidence (FIRE) approach, and who will flexibly tailor implementation strategies to the local ward context, and to resolve barriers and enablers identified. There will be two types of FIRE agents: hospital leaders (hFIRE) and hospital ward nurses (nFIRE). These agents will be allocated to the wards of each hospital. To mitigate the potential risk of facilitators leaving their posts during the study period we will deploy a co-facilitation model with three support nurses on each intervention ward. nFIRE nurses will be appointed to support and train other nurses on the GPC recommendations, carrying out the face-to-face training in their units, working in small groups to review process indicators and routines practices. Both nFIRE and hFIRE will lead an education program based on the theory of planned behavior [43–45] which includes behavioral techniques to facilitate the application of evidence-based practice. At the hospital level, the hFIREs will audit PVC-related practices, identifying barriers and providing support and guidance to resolve such hurdles. The facilitation strategy will be led by expert external facilitators, PREBACP group research, working with both types of FIRE.

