### Data collection

To mitigate control bias, each nurse manager will be provided with information to standardize catheter removal, catheter tip culture, and hemoculture extraction. Tips from all PVC removed from patients experiencing adverse events will be cultured using a semiquantitative method. Clinical, microbiological, and ward information will be collected from each patient on PVC removal.

Project investigators will collect primary and secondary outcome data using a wide range of methods, including questionnaires NWI and EBPQ to nurses, clinical audits monthly, and clinical outcome by requesting statistics report the participating wards at each hospital with the variables. Where these data are not available, clinical outcome data will be adapted from our research to collect the primary and secondary outcome data. Tools will be used for communication between facilitators, auditors, and researchers to collect at the time of activity and throughout the duration of the intervention. The mean hospital length of stay for relevant wards will be collected as reported by the hospital electronic patient management systems. This data collection system was piloted in five of the above hospital units in December 2017. Adverse events will be defined as per international guidelines for the prevention of BSIs (Healthcare Infection Control Practices Advisory Committee, USA, UK, Spain) [46–48]. Three study phases will be planned for the PREBACP study: baseline (2 months), intervention and evaluation (12 months) (Fig. 2).

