### Blinding

Hypothesis and variables will be blind to prevent any selection bias that might arise in the nurses participating in the data collection process. All research assistants will be blinded to group allocation. Success of blinding will be assessed at study end using the James Blinding Index. Although FIREs and intervention wards will not be blinded, control wards will be blinded. Patients will be unaware of the intervention. [name] and [name] analyze the data, all will be blinded to group allocation.

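### The intervention is expected to change the records from which the primary outcome is read, so event capture may differ between arms, in either direction

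*Protocol article*

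**What the plan says.** All references are to the protocol article.

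- **Outcome source.** Primary outcome measures: "This incidence will be determined from evaluation of hospital records at 3, 6, 9, and 12 months". Sample size counts nursing records as the sampling unit. Data collection also mentions statistics reports from the wards and information gathered from each patient when the PVC is removed. It does not rank these sources.
- **Expected change in the records.** Secondary hypotheses predicts for intervention wards "increased documentation about PVC use in nursing records and greater requests of catheter tip culture from PVCs removed from patients experiencing adverse events". Secondary outcome measures makes the percentage of fully completed records an outcome.
- **Blinding.** Intervention wards and FIRE nurses are not blinded; control wards are. Research assistants and analysts are blinded to allocation. Nurses who take part in data collection are to be kept unaware of the hypothesis and variables. The section adds: "Patients will be unaware of the intervention".
- **Standardisation.** Under Data collection, each nurse manager receives information on catheter removal, tip culture and blood culture. The section also states: "Tips from all PVC removed from patients experiencing adverse events will be cultured using a semiquantitative method".
- **Culture-dependent component.** Under Definitions, all three CRBSI types require a positive tip culture. Secondary outcome measures says: "Catheter tip will be measured by number of catheter tip extraction following removal of PVCs".
- **Patient contact.** The intervention includes "leaflets with information for patients and family/careers about peripheral catheters", and under Secondary outcome measures patients are asked whether they know about PVC use and prevention advice.

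**The concern.** A comparison of recorded incidence is fair only if a true event has the same chance of being recorded in both arms. Here the trial itself expects one arm to keep fuller PVC records, and staff on those wards know they are receiving the intervention. Abstraction by blinded assistants protects the step from record to dataset. It does not protect the step from bedside to record. The nurse-manager information covers removal and culture, and does not cover the noting of phlebitis, extravasation or obstruction.

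The bias can run either way:

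- Better capture of events on intervention wards would hide a real benefit.
- Better charting of uneventful catheters would enlarge the denominator and exaggerate benefit. Under-recording of events by staff who know the aim of the programme would do the same.

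A second, smaller problem concerns tip culture. If all tips from adverse-event PVCs are cultured in both arms, the hypothesised excess of requests on intervention wards cannot arise as a difference in practice. If they are not all cultured, detection of CRBSI may differ by arm. A plain count also falls when adverse events fall, even if culturing practice is unchanged.

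**Working it through.** **Inputs (Sample size).** Global rate 44.1% = 16 + 6.8 + 18.1 + 3.2 (phlebitis, obstruction, extravasation, CRBSI). Reduction 15%, two-sided alpha 0.05, power 0.80, 10% missing data, design effect 1.99, final N 3821.

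**Reproducing the plan's figure.** Read as a relative reduction, 15% gives 0.441 × 0.85 = 0.375. The two-proportion formula with pooled variance and no continuity correction gives 866 per arm, 1732 in total. 1732 / 0.90 = 1925, against 1920 stated. 1920 × 1.99 = 3820.8, that is 3821. An absolute 15-point reduction would give only 358, so the relative reading is the one behind the plan.

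**Share that depends on bedside recording.** 16 + 6.8 + 18.1 = 40.9 of 44.1 points. CRBSI is the other 3.2.

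**Effect of unequal capture.** Let r be the probability that a true event is recorded on intervention wards divided by that on control wards. The observed risk ratio is 0.85 × r. The documents give no value for r, so the values below are assumptions. The observed control rate is held at 44.1%. Effective size per arm is 3821 × 0.90 / 1.99 / 2 = 864.

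| r | Observed intervention rate | Observed risk ratio | Power |
|---|---|---|---|
| 1.00 | 37.5% | 0.850 | 80% |
| 1.02 | 38.2% | 0.867 | 70% |
| 1.05 | 39.4% | 0.893 | 52% |
| 1.10 | 41.2% | 0.935 | 23% |
| 1.15 | 43.1% | 0.978 | 6% |
| 1/0.85 = 1.176 | 44.1% | 1.000 | no reduction seen |

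As an example of the last row, capture of 80% on control wards and 94% on intervention wards gives 0.441 × 0.80 = 35.3% and 0.375 × 0.94 = 35.2%.

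The same identity works in the other direction. With r = 0.95 the observed risk ratio is 0.85 × 0.95 = 0.81, so a 15% reduction appears as 19%. With no true effect, r = 0.85 would produce the whole planned reduction.

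**Culture route alone.** Suppose capture differs only for CRBSI. The other components contribute (0.441 − 0.032) × 0.85 = 0.348. If CRBSI also falls by 15%, it contributes 0.032 × 0.85 = 0.0272 times a detection multiplier m. The whole effect is cancelled when m = (0.441 − 0.348) / 0.0272, about 3.4. At m = 2 the observed rate is 40.2% and power about 37%. If the intervention does not change true CRBSI, the cancelling multiplier is (0.441 − 0.348) / 0.032, about 2.9. Either needs a very large difference in detection, although tips are to be cultured only in patients who already have an adverse event.

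**The case against.** The strongest reply is that the article does not say event capture will differ. The hypothesis concerns documentation of PVC use, measured as completeness of records, and fuller records need not contain more events. The article does not say who writes the event entry; that ward nurses do so is inferred from the use of nursing records. It does set out blinded research assistants and analysts, data-collecting nurses unaware of the hypothesis, and standardised removal and culture. No capture rate is given, so the figures show what is possible, not what is likely. All of this stands, and it is why the point is put conditionally. What remains is that none of these safeguards makes the source entry on an unblinded ward independent of allocation.

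Four stronger readings are tempting but unsupported:

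- **That the bias runs towards no effect.** A larger denominator or under-recording would push it the other way.
- **That culture matters as much as charting.** It touches 3.2 of 44.1 points.
- **That the intervention's own leaders score the outcome audits.** The text after Fig. 1 says "the hFIREs will audit PVC-related practices", but as part of finding barriers and giving support. The monthly outcome audits are not assigned to them, and Data collection lists facilitators and auditors separately.
- **That the leaflets disprove the statement about patients.** It can mean that patients do not know their ward's allocation, which a leaflet on catheter care need not reveal. A clarification is enough.

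**Conclusion.** The concern holds as a design weakness, not as a demonstrated bias. The source of the primary outcome is one the trial expects its intervention to alter, on wards that are not blinded, and the stated safeguards act after or beside the point where an event is charted.

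The trial has little tolerance for this. On its own planning figures, a relative difference in capture of 5% to 10% takes power from 80% to between about 52% and 23%, and about 18% removes the effect. These results assume that capture ratios in this range occur and accept the stated design effect of 1.99. They show only the masking direction; the opposite direction is equally open.

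The mismatch between culturing all tips from adverse-event PVCs and expecting more requests on intervention wards, and the unsuitability of a count, follow from the text without assumptions. They affect mainly a secondary outcome.

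**What to change.** 1. **Primary source.** Name the information already gathered from each patient at PVC removal as the source of the primary outcome, on one identical form in both arms. Have events classified against the article's own Definitions by people blinded to allocation, and keep routine records as back-up. State as a residual limitation that recognition at the bedside on unblinded wards still feeds the form.
2. **Supporting analyses.** Add a sensitivity analysis that leaves out the culture-dependent (CRBSI) events. Report documentation completeness by arm descriptively. Do not adjust for it or restrict on it: it is measured after randomisation and the intervention is expected to change it, so conditioning on it could itself bias the comparison.
3. **Tip culture.** Report the proportion of adverse-event PVCs whose tip was cultured, by arm, in place of the count. Reconcile the hypothesis of greater requests with the Data collection statement that all such tips are cultured.
4. **Patient blinding.** Say whether patients are unaware of the allocation or of the intervention itself, given the leaflets and the questions put to them.

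The cost is mainly wording, one common form and one extra analysis. The collection at removal is already planned. The article does not assign event classification to the blinded research assistants, so some staff time must be found for it.
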